**Figure 1 F1:**
[figure not shown]
Program implementation and study timeline.

To be eligible for the program, patients must be ≥ 18 years of age, homeless or unstably housed (38), have ≥ 3 ED presentations, or ≥ 2 hospitalizations within the past year. While definitions of high acute care use vary, we chose the most conservative definition (18) in order to make the program inclusive and allow refinement to occur over the initial phases of implementation. Preliminary data gathered for the first 127 patients referred to the program before expansion indicates that, on average, C2C patients had 9 ED visits in the year prior to referral and 20% had a hospital admission. The most common reasons for admission were cellulitis, sepsis, pneumonia, substance use and other mental health diagnoses. C2C patients were more likely to be male (66%), 29% identified as Indigenous, 88% used substances and 78% were homeless. Referrals are accepted from acute care facilities, health clinics, and community agencies. Reasons for referral include attachment to primary care, housing support, connection to substance use treatment, advocacy, and discharge planning.

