### Measures of Effectiveness

#### Acute Care Use

We will use administrative health data to assess acute care use among C2C patients 12-months before and after enrolment: ED visits (primary outcome); hospital admissions; repeat ED visits within 72 h of discharge; unplanned readmissions within 30 days among hospitalized patients; total hospital bed days; deaths; ED and hospital discharge diagnoses; and ICU admissions. Data will be obtained by linking unique provincial health insurance numbers to administrative health data housed by Alberta Health Services.

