#### Within-Subject Comparison

In a within-subject comparison, patients serve as their own controls, eliminating the need to account for confounding due to immutable patient factors. However, observed changes in use may be due to other factors such as changes in health status over time or concomitant interventions. We will use generalized linear mixed-effects models with a negative binomial distribution to examine the ED visit rate, hospitalization rate, 30-day readmission rate and cumulative hospital bed days over the two time periods (12 months before and after enrolment), adjusting for age, sex, ethnicity, and comorbidities. We will use one-way repeated measures ANOVA to assess changes in patient-reported outcomes. We will perform stratified analyses based on phase at time of enrolment and by pre-program ED visit rate.

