#### Comparison Cohort

We will identify a contemporaneous comparison cohort using administrative health data for a population not enrolled in the C2C program and who have an ED visit or hospital admission with an associated ICD-10 Z59x diagnosis (problems related to housing and economic circumstances) and at least one visit to a Calgary facility between 2014 and 2019. We will use propensity score matching to create a control group from this population. Propensity scores will be calculated for both the C2C and control cohorts and controls will be matched to C2C enrolled clients. This allows us to account for the covariates that may predict C2C enrolment, approximating random assignment and reducing selection bias between the groups. We will use a generalized linear modeling framework to estimate the effect of C2C enrolment on acute care utilization and death rates between these two groups.

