#### Power Calculation

We calculated power for the within-subject comparison for the primary outcome of ED visit rate over 12 months. Under ideal conditions intensive case management with outreach may reduce ED visits by 30% in high users (18). Assuming a mean pre-intervention rate of 9.3 visits/year (as noted for Phase 1 patients) and a post-intervention rate of 6.5 visits/year, a common standard deviation of 10, and a correlation between paired observations of 0.05, a sample of 257 individuals will provide more than 90% power to detect a difference at the 5% level of significance. Note that if the correlation increases, the power will increase, hence our choice of a low correlation. We have a waiver of consent to access administrative health data; therefore all patients that engage with the C2C team are eligible for inclusion in the administrative data analysis. Given our use of administrative data with full capture for participants in Alberta, any loss to follow up will be due to outmigration or invalid personal health insurance numbers. Despite this expected attrition, with 249 engaged patients in July 2018, by end of 2019, we will have an adequate study sample to detect meaningful differences.

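### The matched-cohort outcome model states no adjustment for each person's pre-index count of the outcome, so imbalance in prior use left by the match would bias the rate ratio

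*Protocol article*

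**What the plan says.** The Comparison Cohort section draws controls from people not enrolled in C2C who have an ED visit or admission coded Z59x and "at least one visit to a Calgary facility between 2014 and 2019". It matches them to C2C patients on a propensity score and says of this step: "This allows us to account for the covariates that may predict C2C enrolment". The covariates are not named. The section likens the result to randomisation, then applies a generalized linear model "to estimate the effect of C2C enrolment on acute care utilization and death rates between these two groups". It mentions no baseline count, period term or covariate for that model.

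The neighbouring text differs on three points:

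- **Entry to C2C.** Patients must "have ≥ 3 ED presentations, or ≥ 2 hospitalizations within the past year" (eligibility paragraph after Figure 1). The control pool as described has no such threshold, although the Population-Level Analysis section applies one to its own Z59x population.
- **Adjustment in the other two approaches.** The within-subject model works "over the two time periods (12 months before and after enrolment), adjusting for age, sex, ethnicity, and comorbidities", and the population-level model also names its adjustment variables. Only the matched model names none.
- **Pre-period data.** The Acute Care Use section uses administrative data "to assess acute care use among C2C patients 12-months before and after enrolment". The pre-period is specified for C2C patients and not mentioned for controls.

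**The concern.** Prior use decides who can enter C2C and is likely to be a strong predictor of later use. The two source populations may start far apart on it, and one scalar score has to close the gap. Even a score that contains prior use balances it only on average, so the matched groups can still differ. The stated model then has nothing to absorb the difference.

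This is the only one of the three approaches with a concurrent control group. The article itself says that changes seen in the within-subject comparison may have other causes, so the matched comparison carries much of the causal argument. If excess prior use remains in the C2C group, the programme looks less effective than it is. The opposite imbalance makes it look more effective. The Discussion concedes unmeasured confounding after matching, but this confounder is measured.

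**Working it through.** **Inputs from Power Calculation.** "Assuming a mean pre-intervention rate of 9.3 visits/year", falling to 6.5 (difference 2.8); SD 10; pre/post correlation ρ = 0.05; n = 257; 5% level, taken as two-sided. No power figure is given for the matched comparison. Its group size is assumed to be 257 per arm at 1:1, with the same difference and SD.

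**1. The article's own figure.** SD of the paired difference = 10 × √(2 × (1 − 0.05)) = 13.78. The normal approximation gives 90.3% power and the noncentral t gives 90.0%, so the stated figure of more than 90% reproduces.

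**2. Precision of the matched contrast.** This is a linear approximation that ignores correlation within matched sets. The post-only standard error is 10 × √(2/257) = 0.882. Power is Φ(2.8/0.882 − 1.96) = 88.8%, and 90% power needs 269 per group. With the pre-index count as a covariate, the variance is multiplied by 1 − ρ². With a change score it is multiplied by 2(1 − ρ).

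| ρ | Covariate: variance factor | Covariate: power | Covariate: n per group for 90% | Change score: power |
|---|---|---|---|---|
| 0.05 (article) | 0.9975 | 88.8% | 268 | 63.4% |
| 0.3 | 0.91 | 91.4% | 244 | 76.5% |
| 0.5 | 0.75 | 95.6% | 202 | 88.8% |
| 0.7 | 0.51 | 99.4% | 137 | 98.4% |

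At the article's correlation the gain is 0.25% of variance. A change score loses precision whenever ρ is below 0.5.

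**3. Bias from a gap in the observed prior count.** With equal SDs, a gap of g visits per year shifts the unadjusted contrast by about ρ × g. For g = 1 (0.1 SD):

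- ρ = 0.05: 0.05 visits, or 0.05/2.8 = 2% of the planned effect
- ρ = 0.3: 0.3 visits, 11%
- ρ = 0.5: 0.5 visits, 18%
- ρ = 0.7: 0.7 visits, 25%

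**4. Bias from a gap in underlying rate.** Here the gap passes straight through: 0.70 × 1.10 = 0.77 and 0.70 × 1.15 = 0.805. Simulated gamma-Poisson counts (257 per group, true rate ratio 0.70, negative binomial regression with and without the log pre-index count) gave the results below. Ranges cover two separate runs. Correlation and imbalance are assumptions.

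| Correlation | Excess rate in C2C | Unadjusted RR | Adjusted RR |
|---|---|---|---|
| about 0.45 | 10% | 0.77–0.78 | 0.73–0.74 |
| about 0.45 | 15% | 0.80–0.81 | 0.75 |
| about 0.31 | 15% | 0.81 | 0.77 |
| 0.13–0.21 | 15% | 0.81 | 0.79–0.80 |

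In the first row, the share of bias removed is (0.77 − 0.73)/(0.77 − 0.70) = 57%. With no imbalance, the ratio of unadjusted to adjusted variance was 1.21 to 1.26 near 0.45, 1.03 to 1.06 near 0.31, and 1.02 to 1.03 at about 0.2 or below.

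**5. With a matching step and a lower-use control pool.** These runs also had a true rate ratio of 0.70.

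- Score contains prior use: in three settings the covariate moved the estimate from 0.85 to 0.83, from 0.93 to 0.91, and from 0.874 to 0.855. In the last, the pool's rate was 1.5-fold lower, a prior-use ratio of about 1.08 remained after matching, and the variance ratio was 0.98.
- Score omits prior use: from 1.04 to 0.82.

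**The case against.** The strongest reply is that the gap is inferred from silence. A reader might infer that the plan ignores prior use altogether, and the article does not support that. It says the score covers predictors of enrolment, and prior use is the entry criterion, hence the most obvious candidate. A condensed article may also leave the covariate list to a fuller plan. This stands. What remains is that the article describes the matched outcome model without adjustment while naming adjustment sets for the other two, and that a score containing prior use can still leave a residual.

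A reader might also infer a material loss of precision. The article's own correlation of 0.05 gives 0.25% of variance. That value is a deliberately low choice and not an estimate, so a larger gain is plausible, but it rests on an assumed correlation.

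A third tempting reading is that any leftover difference passes one-for-one into the rate ratio. That holds for a gap in underlying rate. A gap in the observed count passes through in proportion to ρ.

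The remedy also has limits. If the score already contains prior use, the extra term removed only about a tenth of the error: (0.85 − 0.83)/(0.85 − 0.70) = 13% and (0.93 − 0.91)/(0.93 − 0.70) = 9%. Much of the rest is regression to the mean: controls from a lower-use pool, picked for a high count, fall back towards their own lower average. A covariate does not cure that.

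Finally, this is one of three complementary analyses, and the powered comparison is the within-subject one. That limits the weight of the point but does not remove it.

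**Conclusion.** The point holds as one about bias. The stated matched model has no term for the pre-index count, the control pool lacks the high-use criterion, and a residual gap in prior use is a real risk. Under an assumed 10% excess in underlying rate and a correlation of about 0.45, a true 30% reduction would appear as about 23% unadjusted and 27% adjusted. At 15% it would appear as about 20% and 25%. If the score already includes prior use, the covariate adds little. If it does not, the error is large and the covariate removes much of it: (1.04 − 0.82)/(1.04 − 0.70) = 65%.

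Adjustment moved the estimate towards the truth in every imbalanced setting tried, with no material loss of precision. The correction is partial throughout. The precision gain runs from negligible at 0.05 to a variance ratio of about 1.2 at 0.45. The size of the imbalance and every correlation above 0.05 are assumptions; the article gives neither. The change is worth making, but its absence does not invalidate the evaluation.

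**What to change.** 1. State that 12-month pre-index ED visits and admissions enter the propensity score.
2. Add each person's 12-month pre-index count of the same outcome, on the log scale (for example the log of count plus one), to the matched outcome model for ED visits, admissions and bed days. For deaths, which have no prior count, use pre-index ED visits and admissions.
3. Enter the count as a covariate and not as a change score, which loses precision when the correlation is below 0.5.
4. Cluster standard errors on the matched set.
5. Keep the unadjusted matched contrast as a sensitivity analysis, and say in the report that adjustment corrects residual imbalance only in part.

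The cost is one model term and a sentence or two of text. The counts come from the same administrative source, from which the Population-Level Analysis section already plans to take prior 12-month use for Z59x-coded patients. Each control needs an index date, which the 12-month outcome window requires in any case.

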#### Population-Level Analysis

Phased implementation provides an opportunity to examine trends in acute care use using administrative data for the target population as a whole. With increased reach of C2C in Calgary with each phase, the proportion of the target population exposed to C2C will increase over time, and, if successful, acute care use in this population will, on average, decrease over time. We will select a population of patients from administrative health data who present to a Calgary acute care facility and meet the following criteria: ≥ 18 years of age; ED visit or hospital admission with an associated ICD-10 Z59x diagnosis (problems related to housing and economic circumstances); ≥ 3 ED presentations, or ≥ 2 hospitalizations within the past year; and at least one high-risk health condition, as defined by ICD-10 diagnostic codes corresponding to C2C enrolment criteria.

Beginning 6 months prior to C2C program implementation, and continuing for 12 months beyond enrolment end date (i.e., May 2015–December 2020), we will retrospectively ascertain the following every 3 months: total number of patients meeting eligibility (per administrative data as above); proportion of patients currently or previously enrolled in C2C (per program data); acute care use for the prior 12 months. We will inspect the number of eligible patients enrolled in C2C over time to ensure our increased enrolment assumption is correct. We will use a generalized linear modeling framework to assess the trend over time, in both the total number of eligible patients in administrative data (to assess change in the absolute number) and average acute care use (to assess change in use among those who meet criteria), measured at 3-month intervals. We will adjust for age, sex and defined health conditions.

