## Methods and Analysis

### Study Setting

Calgary, Alberta, the fourth largest city in Canada, experienced significant changes leading up to and during the implementation of Connect 2 Care (33, 34). Calgary's population grew by 25% to 1,596,248 over the preceding decade (33). Following exponential growth in homelessness between 1992 and 2008 (34), Calgary's homeless population remained stable and in 2016, when we began this work, the point prevalence of homeless individuals in Calgary was estimated at 3,430 (35). At the time, the rental vacancy rate in Calgary was 7.0% and the average and median market rents were $1,150 CAD/month and $1,120 CAD/month, respectively (36). Additionally, Calgary and Alberta are facing an ongoing opioid overdose epidemic; Alberta has the second highest incidence of opioid poisonings in Canada, with substantial increases in associated ED visits and hospital admissions (37).

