### The Connect 2 Care Intervention

C2C is a multidisciplinary mobile outreach team that provides transitional case management, advocacy, and care navigation for socially vulnerable patients. Clinical and operational leadership at CUPS developed the C2C pilot, launched with two registered nurses (RNs) in November 2015, in partnership with Foothills Medical Center, the largest of four tertiary care hospitals in Calgary. With innovation grant funding, we expanded the program across three implementation phases (see Figure 1). In Phase 1 (January–December 2017) two HNs were added; in Phase 2 (January–December 2018) the referral base expanded to all four Calgary hospitals, as well as community agencies, using two additional HNs; in Phase 3 (January–December 2019), the program reached maturity with 2 RNs and 4 HNs. HNs are hired from a pool of emergency shelter outreach workers at Calgary Alpha House Society, a housing, shelter, outreach, and detoxification facility. HNs are acquainted with the target population's social and community context and are provided health and health system navigation training. Collectively, the C2C team has expertise in chronic disease management, mental health, harm reduction and addictions, as well as extensive knowledge of social programs, community health, housing, financial and transportation resources.

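### The population-level time trend rests on overlapping 12-month look-backs, almost no pre-launch baseline and no programme term, so it cannot isolate C2C and needs an error model that allows for the overlap

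*Protocol article*

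**What the plan says.** The Population-Level Analysis section of the protocol article fixes these features:

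- **Spacing and outcome window.** "we will retrospectively ascertain the following every 3 months", with the use outcome defined as "acute care use for the prior 12 months".
- **Eligibility window.** Patients qualify at each point on their emergency department visits or "hospitalizations within the past year; and at least one high-risk health condition", so the count of eligible patients also looks back a year.
- **Span.** "Beginning 6 months prior to C2C program implementation", and "continuing for 12 months beyond enrolment end date (i.e., May 2015–December 2020". The section on the intervention dates the pilot: it was "launched with two registered nurses (RNs) in November 2015".
- **Model.** A generalized linear model for the time trend in two outcomes, the number eligible and their average use, adjusted for age, sex and health conditions. No correlation structure is named, and no launch, phase or exposure term.
- **Exposure.** The proportion ever enrolled is recorded at every point. The one stated use of enrolment data is this: "We will inspect the number of eligible patients enrolled in C2C over time to ensure our increased enrolment assumption is correct".

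The within-subject analysis and the cost analysis name mixed or random effects. This analysis does not.

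**The concern.** The rationale for this analysis is that C2C reaches more of the target population with each phase, so average use should fall. Three stated choices work against testing that.

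First, a 12-month total taken every 3 months reuses most of its data from point to point, so 23 points carry much less than 23 points' worth of information. Second, a series that starts six months before launch gives almost nothing from which to estimate the trend that would have continued without the programme. Third, a slope on calendar time measures everything that changed in Calgary between 2015 and 2020, not C2C alone. The Study Setting section itself describes an opioid epidemic "with substantial increases in associated ED visits and hospital admissions".

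At stake is whether one of the three complementary effectiveness analyses can be interpreted, both in its p-value and in what its slope is attributed to.

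**Working it through.** **The plan's own figure.** None is given for this analysis. The only power figure is for the within-subject comparison: SD of the difference = 10 × √(2 × (1 − 0.05)) = 13.78; z = 2.8 / (13.78/√257) = 3.26; power = Φ(3.26 − 1.96) = 90.3%. The stated power of more than 90% with 257 patients reproduces, and nothing below affects it.

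**1. Number of points.** May 2015 to November 2020 is 66 months, so 66/3 + 1 = 23 points.

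**2. Overlap.** Windows k quarters apart share 12 − 3k months. If quarters are independent with equal variance, the correlation is (4 − k)/4, that is 0.75, 0.50 and 0.25 at lags 1 to 3, then zero.

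**3. Standard error of the slope if the points are treated as independent.** For a long series the variance inflation is 1 + 2 × (0.75 + 0.50 + 0.25) = 4, a factor of 2 on the standard error. For 23 points, √(t′Rt / t′t), with t the centred time index and R the correlation matrix above, gives 1.83 when the marginal variance is known. In practice the residual variance is estimated from the same correlated series and is also too small. In 40,000 simulated trendless series per row (ordinary least-squares slope, t-test at 5%):

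| Outcome at 23 points | Correlation between quarters | Mean naive SE / true SE | Rejection at 5% |
|---|---|---|---|
| 12-month look-back | 0 | 0.46 | 35% |
| 12-month look-back | 0.2 | 0.43 | 39% |
| 12-month look-back | 0.4 | 0.39 | 43% |
| Separate 3-month counts | 0 | 0.99 | 4.9% |
| Separate 3-month counts | 0.2 | 0.81 | 10% |
| Separate 3-month counts | 0.4 | 0.65 | 18% |

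With 22 or 24 points the first row hardly moves (0.46; 36% and 35%).

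**4. Patient-level rows treated as independent.** This needs figures that the article does not give. I assumed 300 patients per point and gamma-Poisson counts with mean 9.3 and SD 10 (the values in the power calculation), and varied the share of patients replaced each quarter, with 1,000 simulations each. The ratio of naive to true standard error was 0.46 at 12.5% turnover, 0.49 at 25% and 0.63 at 50%, but 1.70 with no turnover. In that closed cohort, stable differences between patients inflate the naive residual variance yet cancel out of the slope.

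**5. Baseline.** Taking each point at the start of its month:

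- May 2015 covers May 2014 to April 2015, and August 2015 covers August 2014 to July 2015. They share nine months, so their difference is only May–July 2015 minus May–July 2014.
- November 2015 falls in the launch month. Counting it gives three heavily overlapping pre-launch points.
- The February, May and August 2016 windows contain 9, 6 and 3 months of pre-launch use, which blurs any change at launch.

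**6. Attribution.** With time, age, sex and health conditions as the only stated terms, the time coefficient is programme effect plus secular change, and nothing in the model separates them.

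**The case against.** The strongest reply is that the article never says the points are treated as independent. A generalized linear model can be fitted with estimating equations, robust errors or an autocorrelation correction, and such detail is commonly left to an analysis plan. This stands. A reader might infer that the planned standard errors are half their true size and that the test will often be falsely significant. The documents do not support that as a fact: it follows only under independent errors on the aggregate series. Adjustment for age, sex and health conditions is compatible with patient-level rows, where the direction of the error depends on a turnover that is not given.

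A reader might also infer that the opioid-related increase would be mistaken for a programme effect. The direction is the opposite: C2C is expected to lower use, so a secular rise would mask a benefit, while a secular fall would mimic one.

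It can further be said that seven points (May 2015 to November 2016) precede the January 2017 expansion and form a low-exposure baseline, that the article admits confounding that changes with time, and that the matched contemporaneous cohort addresses secular change. Each is fair. But the low-exposure points follow the pilot launch in part, an admitted limitation does not repair the model, and the matched cohort belongs to a different analysis. Finally, the article's silence on other uses of the enrolled proportion does not prove there are none. What can be said is that no such use is stated.

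**Conclusion.** The point holds in conditional form. The overlap, the near-absent pre-launch baseline and the calendar-time slope are choices the article states, not details left out. A later analysis plan could correct the variance, but it could not obtain a baseline or remove the overlap without changing this text.

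- **Precision.** Under independent errors on 23 aggregate points with independent quarters, the standard error is about 0.46 of its true size and the 5% test rejects about 35% of the time. Positive correlation between quarters makes this worse. For patient-level rows the ratio ran from 0.46 to 1.70 under my assumptions, so neither size nor direction can be fixed from the article.
- **Baseline and attribution.** These do not depend on the error model. A pre-programme trend is practically not estimable from two or three overlapping points, and the stated model cannot separate C2C from secular change.

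This concerns one of three complementary analyses. The primary within-subject comparison is untouched.

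**What to change.** 1. Make the use outcome a non-overlapping 3-month count, with patient-clustered errors for patient rows or autocorrelation-robust errors for an aggregate series. Separate quarters alone are not enough: the table shows 10% to 18% rejection if correlation of 0.2 to 0.4 remains unmodelled.
2. Keep the past-year window for the eligible count, since it defines the population, but use errors that allow for dependence over at least the three lags created by the overlap.
3. Start the series earlier where the administrative data allow. Beginning in May 2014, for example, adds four pre-launch points and needs data from May 2013 for the eligibility look-back. The Comparison Cohort section mentions 2014, but only as a visit criterion for another cohort, so it does not establish that such an extract exists.
4. Enter either phase terms or the already collected enrolled proportion in the model. Do not enter all of them together with time: they rise together, and their effects would be collinear.

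The cost is revised analysis wording, a somewhat longer extract, noisier quarterly counts and wider confidence intervals.

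### The population-level trend rests on recorded Z59x codes, with no window for the code and no check on coding frequency, so it cannot separate a coding change from a C2C effect

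*Protocol article*

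**What the plan says.** The Population-Level Analysis section of the Protocol article selects adults with an "ED visit or hospital admission with an associated ICD-10 Z59x diagnosis (problems related to housing and economic circumstances"), who also have "≥ 3 ED presentations, or ≥ 2 hospitalizations within the past year" and at least one high-risk condition. The one-year window is attached to the use threshold. The Z59x criterion is listed separately and carries no window.

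Eligibility is rebuilt at each quarterly point ("i.e., May 2015–December 2020), we will retrospectively ascertain the following every 3 months"). The use outcome has its own fixed window, "acute care use for the prior 12 months". Two quantities are trended. The model is to "assess the trend over time, in both the total number of eligible patients in administrative data (to assess change in the absolute number"), and also in "average acute care use (to assess change in use among those who meet criteria), measured at 3-month intervals". The section expects average use in this population to fall if the program works. The model adjusts for age, sex and defined health conditions. The one assumption to be checked is that C2C enrolment grows.

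The program itself spread during the series. It began with one hospital, and in 2018 "the referral base expanded to all four Calgary hospitals, as well as community agencies, using two additional HNs" (The Connect 2 Care Intervention).

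**The concern.** A trend is interpretable only if the rule that finds patients works equally well at every time point. Here the rule depends on whether someone recorded a housing code, and nothing in the model or the stated checks measures whether that habit changed. No comparison series is described that would share the coding change without sharing the program.

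More complete coding brings in people who were always eligible in fact but were not found before. The count then rises. If those newly found are lighter users than those already found, the average falls, and the section treats a falling average as the sign of success.

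The signal sought is also diluted, because only part of the eligible population is ever enrolled. A modest artefact could therefore be as large as the effect.

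**Working it through.** **Plan's own figure.** The population-level section states no effect size or power. The only power figure is for the within-subject comparison: SD of the difference = 10 × √(2 × (1 − 0.05)) = 13.78, difference 9.3 − 6.5 = 2.8, n = 257, two-sided 5%, giving power of 0.90. It reproduces but has no bearing on this point.

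**Inputs.**
- From the protocol: entry needs at least 3 ED visits in the year and a Z59x code; the series runs 68 calendar months.
- Assumed, because the documents give no figures: the probability q that any one visit carries the code, and the visit distribution in the administrative population. I used negative binomial distributions with five mean/SD pairs: 9.3/10 (the values in the Power Calculation section, which describe C2C patients), 9.3/8.5, 8/8, 5/7 and 3/5.
- Not modelled: entry through hospitalizations, and the health-condition criterion.

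**Model.** C2C has no effect, true use is constant and the code window is a fixed 12 months. A patient with n visits is found with probability 1 − (1 − q)^n. The eligible count is proportional to Σ P(n)[1 − (1 − q)^n] over n ≥ 3. Average use is the mean of n under those weights.

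**Why the average can fall.** At q = 0.05 a 3-visit patient is found with probability 1 − 0.95³ = 0.143 and a 20-visit patient with 1 − 0.95²⁰ = 0.642. At q = 0.10 these become 0.271 and 0.878. Capture rises by a factor of 1.90 in the lighter user and 1.37 in the heavier one, so the mix shifts towards lighter users.

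**Results, every visit equally likely to be coded** (count per 1,000 people in the underlying distribution; mean visits per year):

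| Mean/SD | q = 0.05 | q = 0.08 | q = 0.10 |
|---|---|---|---|
| 9.3/10 | 303; 17.2 | 404; 16.1 | 453; 15.5 |
| 5/7 | 171; 13.4 | 235; 12.6 | 269; 12.2 |
| 3/5 | 103; 11.0 | 146; 10.4 | 169; 10.1 |

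Across all five distributions:
- q from 0.05 to 0.08: count +33% to +41%, average use −5.4% to −6.5%.
- q from 0.05 to 0.10: count +50% to +63%, average use −8% to −10%.

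**Counter-case: coding improves only in patients with 10 or more visits** (others stay at 0.05), same five distributions:
- to 0.10: count +21% to +28%, average use 0% to +6%.
- to 0.20: count +36% to +46%, average use −1% to +8%.

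If capture is unrelated to the number of visits, the count rises and the average does not move. The rise in count held in every scenario; the fall in average use did not.

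**Scale of the signal sought.** The Power Calculation section gives 249 engaged patients in July 2018 and a 30% reduction under ideal conditions. The size of the eligible population is not given. Assume it is 1,000, or 3,430 (the homeless point prevalence under Study Setting, used only as a bound), and that enrolled patients have average use. The whole-population change is then 0.30 × 249/1,000 = 7.5%, or 0.30 × 249/3,430 = 2.2%. If it were only 500, the change would be 0.30 × 249/500 = 15%. Enrolment continued after July 2018, so later figures would be larger.

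**The case against.** **A condensed article may leave the code window to the full protocol.** This is fair for the window alone. A reader might infer that any earlier code qualifies, so that the look-back lengthens at each quarterly point and inflates the count by itself. The documents do not support that as a finding. The text is silent, and a code at the current presentation or within the past year fits it equally well. The 2014 start that such a reading needs ("at least one visit to a Calgary facility between 2014 and 2019") belongs to the Comparison Cohort section, a different analysis. The point stands without it, because coding drift remains under a fixed window.

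**Average use need not fall.** This also stands. A reader might infer that better coding lowers average use whatever C2C does, but the counter-case shows it can stay flat or rise. If staff record housing because they are referring frequent attenders to C2C, that is the direction to expect.

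**No passage says that C2C changed coding.** Correct. The spread of referral to four hospitals gives a reason to expect it, but that is inference. The criticism is that the plan could not detect such a change, not that one is known to have occurred.

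**The two artefacts pull in opposite directions.** A higher count does not look like benefit, while a lower average does. Since both are reported, a rising count beside a falling mean would be a visible warning. That helps a careful reader, but the plan attaches no rule to it.

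**This is a supporting analysis.** It is one of three complementary approaches, and the article says each has interpretive caveats. The limitations mention time-varying confounders in general, but not coding. The powered comparison does not use Z59x.

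**Conclusion.** The concern holds in a limited form. As written, the population-level analysis is an uncontrolled trend in patients found only through a recorded code, and it cannot distinguish more complete coding from a program effect. With no C2C effect, more complete coding raised the eligible count in every scenario tested. Average use can fall by about 5% to 10% if the per-visit coding probability rises from 0.05 to 0.08–0.10 and every visit has an equal chance of being coded. That is of the same order as a diluted program effect of about 2% to 7.5%, given an eligible population of 1,000 to 3,430. The coding probabilities, visit distributions and population sizes are all assumptions. The direction of bias in average use is not fixed. The effect on interpretation is confined to this supporting analysis.

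**What to change.** In the Population-Level Analysis section of the Protocol article:

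1. Require the Z59x code within the same prior 12 months at every quarterly point. This rules out look-back drift but leaves coding drift.
2. Report the frequency of Z59x coding over time, for instance as the share of encounters carrying the code among adults who meet the use and health-condition criteria, by quarter and hospital. Keep this descriptive, since the share also moves if homelessness itself changes.
3. Do not use the share of C2C enrolees with a code as a correction factor. Referral sources changed between phases, and there are no enrolees before November 2015. Numbers are also small: if the 249 patients are counted from launch, about 32 months, that is roughly 23 per quarter, and a share of 40% would have a standard error of √(0.4 × 0.6/23) = 10 percentage points.
4. Repeat both trends, as a sensitivity analysis, in a population defined by age, use thresholds and high-risk condition, without Z59x.
5. State in advance that if coding frequency shifts, or the two series disagree, the population-level trends will be reported as descriptive and not attributed to C2C.

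The cost is a few sentences and some additional runs on administrative data, with no new data collection from patients. The fixed window gives a smaller series. The population without Z59x is less specific to the target group and dilutes any C2C effect, so disagreement between the series calls for caution and does not prove that coding changed.
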